# SYNOPSIS

| **COMPOUND:** Coarsucam® | **STUDY No.: ARAMF_L_02661** |
| --- | --- |
| TITLE | A randomised study to compare a fixed dose combination of artesunate plus amodiaquine versus a fixed dose combination of artemether plus lumefantrine in treatment of repeated uncomplicated *Plasmodium falciparum* malaria attacks occurring during 2 years of follow-up, in children in Uganda |
| TRIAL LOCATION  Principal investigator | [name]; Uganda |
| STUDY OBJECTIVE(S) | **Primary:**  To demonstrate the non-inferiority of PCR adjusted adequate clinical and parasitological response at D28 (WHO protocol in vivo D28 2003) of Coarsucam® (artesunate plus amodiaquine) versus Coartem® (artemether plus lumefantrine), based on the first malaria attack of each patient.  **Secondary:**  **For the first attack** (directly observed administration)**:**  To compare the two groups of treatment in terms of:   - D42 efficacy - Parasitological and fever clearance - Clinical and biological tolerability - Evolution of gametocyte carriage   **For repeated attacks**: (non observed administration )  To compare the two groups of treatment in terms of:   - D28 and D42 clinical and parasitological effectiveness - Clinical and biological tolerability - Proportion of patients without fever at D3 - Proportion of patients without parasite at D3 - Evolution of gametocyte carriage - Compliance   **During the total follow up of the cohort**  To compare the two groups of treatment in terms of:   - Treatment incidence density - Impact of repeated treatment on clinical and biological tolerability - Impact on anemia - Evolution of Hackett score |
| STUDY DESIGN | An open randomised, comparative, Phase IV trial |
| STUDY POPULATION |  |
| Specific selection criteria for initial inclusion in the cohort:  Main selection criteria for each attack: | - Children 6 to 59 months - Confirmed mono infection with *Plasmodium falciparum* with parasitemia ≥2000 asexual parasites /µl of blood - No movement from the investigator site area planned throughout the 2-year duration of the trial - No allergy to one of the study drugs - No concomitant febrile illness - Written informed consent of the parents /legal representative - Body weight ≥5 kg - Confirmed *Plasmodium falciparum* infection with positive parasitemia - Able to be treated by oral route - Fever (Axillary temperature ≥ 37,5°C) at D0 or history of fever in the previous 24 hours - Agreement to comply with the study protocol - No danger signs of malaria - No other severe illnesses or underlying diseases - No treatment with artesunate +amodiaquine or artemether-lumefantrine within the previous 2 weeks.   No participation in another ongoing clinical study |
| Total expected number of patients: | 400 patients, 200 per arm |
| Expected number of sites: | 1, Nagongera Health Centre IV, Tororo district |
| INVESTIGATIONAL PRODUCT(S) | **Coarsucam**®, fixed combination of artesunate (AS) and amodiaquine (AQ) |
| Formulation(s): | Infants tablets: AS 25/AQ 67,5 mg  Toddlers tablets: AS 50/AQ 135 mg  Children tablets: AS 100/AQ 270 mg |
| Route(s) of administration: | Oral route  Supervised administration for the first attack  Unsupervised administrations for following attacks (except for the 1st intake) |
| Dose regimen:  COMPARATOR | Once daily, dose according to bodyweight range  Duration of treatment: 3days  **Coartem®** (arthemether+ lumefantrine)  Tablets, 20/120 mg, oral route, twice daily, dose according to bodyweight range.  Duration of treatment: 3 days |
| EVALUATION CRITERIA | - PCR corrected and uncorrected clinical and parasitological cure rate at D28 and D42 ( WHO classification) - Fever and parasitological clearance (for the 1st attack) by measuring the axillary temperature and monitoring parasitemia - Proportion of afebrile patients at D3 and proportion of patients without parasites at D3 (for following attacks) - Clinical efficacy : evolution of baseline symptoms (all clinical symptoms will be graded) - Compliance based on number of residual tablets in blisters - Treatment incidence density during the 2 years of follow up (comparison of the number of malaria attacks between the two arms during the 2 years) - Mean delay between 2 attacks during the 2 years of follow up - Clinical tolerability ( incidence and intensity of recorded AE ) - Biological tolerability (Hb, Bilirubin, ALAT, Creatinine, Leukocytes, Neutrophils, and Platelets count) |
| RESCUE TREATMENT | Because PCR will not be available in real time:  Any failure before D14, will be considered as a recrudescence and will receive rescue treatment  Failure at D14 or later will be considered as reinfection; and the same ACT treatment will be repeated |
| ASSESSMENT SCHEDULE | Refer to flowchart |
| STATISTICAL CONSIDERATIONS | **Number of patients:**  With a non-inferiority margin () chosen at 5 %, =5%, and  =20%, and the hypothesis of 97% of success rate with Coartem®, 174 patients are requested; taking account of 15% of lost follow-up 200 patients are needed per treatment group.  **Statistical generalities**  All statistical analyses will be performed on SAS software (version 8.2 for PC).  All statistical tests will be bilateral and performed at a 5% significance level excepted for the non-inferiority analysis (unilateral confidence interval)  **Efficacy Analysis**  The non-inferiority of PCR adjusted adequate clinical and parasitological response at D28 (WHO protocol in vivo D28 2003) of Coarsucam® (artesunate plus amodiaquine) versus Coartem® (artemether plus lumefantrine), based on the first malaria attack of each patient will be studied using the 95% one-sided confidence interval on ITT and Per Protocol populations. |
| DURATION OF STUDY PERIOD | 2 years  Each attack will be actively followed for 42 days |

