**During the total follow up of the cohort**

To compare the two groups of treatment in terms of:

- Treatment incidence density
- Impact of repeated treatment on clinical and biological tolerability
- Impact on anaemia
- Impact on Hackett score

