## Duration of study

Thescheduled duration of the study is 2 years. Each malaria attack that occurs during this period will be followed for 42 days.

Each new malaria attack occurring at least 14 days after the previous one will be considered as a reinfection, will be therefore treated with the same drug and followed up during 42 days.

All patients presenting to the study clinic with a new episode of fever will undergo standard evaluation (history, physical examination and Giemsa-stained blood smear) for the diagnosis of malaria. Participants will be randomized to one of two combination treatment regimens at the time of their first diagnosis of uncomplicated malaria. Each patient will be followed up actively after recruitment for 42 days (first follow up) and then passively for 2 years. If within the 2-year period the patient presents with a new malaria attack, he/she will be enrolled again in the study. At each episode the patient will receive the same drug.

Participants will be followed for 2 years for all routine medical care in the study clinic. All subsequent episodes of uncomplicated malaria will be treated with each participant’s assigned treatment regimen. All clinical treatment failures occurring within 14 days of diagnosis and all episodes of complicated malaria will be treated with quinine, the standard therapy for malaria after treatment failure in Uganda. All episodes diagnosed more than 14 days after a previous episode will be considered new episodes for treatment purposes.

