# Selection of patients

## Number of patients planned

Two hundred patients will be enrolled in each group. The duration of the study will be 2 years starting from the enrollment date of the first patient. We anticipate that all the study patients shall be recruited within four months. Once patients have been assigned to a given study drug, each new episode of uncomplicated malaria, occurring after a delay of 14 days, will be retreated with the same treatment previously used.

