### Secondary criteria

For the first episode:

- Clinical and parasitological efficacy is defined by grading clinical signs further to an interview by the investigator, together with the values obtained for temperature and parasitaemia before and after PCR correction at D42, and before PCR correction at D28
- Monitoring of parasitaemia during the different visits in order to define clearance
- Measure of axillary temperature at each visit in order to define the clearance of fever
- Monitoring of gametocytaemia during each evaluation

For the following episodes:

- Clinical and parasitological effectiveness is defined by grading the clinical signs further to an interview by the investigator, together with the values obtained for temperature and parasitaemia before and after PCR correction at D28 and D42
- Proportion of patients without fever at D3 obtained with the values of temperature (axillary temperature<37.5°C)
- Proportion of patients without parasites at D3 (negative thick smear)

During the total follow up of the cohort:

- Compare the number of malaria attack for each patient between two arms and mean delay between 2 attacks during the 2-years of follow up
- Compare the number of patients with anemia at D0 of each episode during the 2 years per arm.
- Compare the evolution of anaemia by patient between D0 and D28 for each episode

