## Procedure for withdrawal of patients from the cohort

Enrolled patients will be withdrawn from the cohort for the following reasons:

1. Movement out of the study area for > 60 consecutive days
2. Inability to be located for > 60 consecutive days
3. Withdrawal of informed consent
4. Development of any serious adverse event that requires a withdrawal from study
5. Failure to achieve an adequate clinical response after treatment with quinine plus clindamycin except if it was a severe malaria attack requiring parenteral quinine therapy.
6. Unable to comply with the study schedule and procedures
7. Diagnosis of a serious chronic disease requiring frequent medical care.

If a patient is withdrawn for reasons # 1, 2, or 3, we will be unable to perform any additional study procedures, and will not plan to obtain any follow-up tests. If a patient is withdrawn for reasons # 4, 5 or 7, because a serious health problem developed plans to obtain appropriate follow-up tests will be individualized to each patient. If the patient is withdrawn for reason # 6, plans to obtain appropriate follow-up tests, will be individualized to each patient, depending on the health status of the patient at the time of withdrawal, and the willingness of the participant and their parent/guardian to proceed with additional testing.

- All study withdrawals should be recorded by the Investigator in the appropriate pages when considered as confirmed;
- If possible, the patients are assessed using the procedures normally planned on D28 if withdrawal before D28 or using the procedures planned on D42 if withdrawal between D28 and D42.

The Investigator should make every effort to contact the patient, to identify the reason why he/she failed to attend the visit, and to determine his/her health status, including at least his/her vital status.

Patients who did not complete the study and for whom no endpoint data are available will be considered as lost to follow-up. The statistical analysis plan will specify how these patients lost to follow-up for their primary endpoints will be considered.

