#### Secondary efficacy variables

Comparison of both treatment groups in terms of:

- Response to treatment at D28, before PCR correction for the first attack
- Response to treatment at D28, before and after PCR correction for all repeated attacks
- Response to treatment at D42, before and after PCR for each attack
- Time to parasite clearance (proportion of aparasitaemic patients at 24, 48 and 72 hours) for the first attack
- Time to fever clearance (proportion of afebrile patients at 24, 48 and 72 hours) for the first attack
- Proportion of afebrile patients at D3 for the following attacks
- Proportion of patients without parasite at D3 for the following attacks
- Evolution of number of gametocytes carriers during the 42 days of follow-up and for each episode
- Evolution of the mean of gametocytes during the 42 days of follow-up and for each episode
- Evolution of abnormal biological baseline value for each attack
- Number of malaria attacks during the 2 years of follow up (treatment density)
- Evolution of the average duration between 2 attacks during the 2 years of follow up
- Evolution of haemoglobin value for each patient during each attack (between D0 and D28) during the 2 years of follow up
- Evolution of mean haemoglobin values at D0,D3, D7,D14 and D28 for each episode during the 2 years of follow up
- Evolution of Hackett score during the 2 years of follow-up

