#### Analysis of secondary efficacy variables

Non inferiority analysis will be performed on the same way than for the main criterion for

- before PCR corrected cure rate at D28 for the first attack
- before and after PCR corrected cure rate at D28 for the following attacks
- before and after PCR corrected cure rate at D42 for all attacks

An analysis for repeated measurements will be performed. A model will be built in order to explain the success/failure of the response. The rank of the attack, the group of treatment and their interaction will be included in the model. Some other relevant parameters could be included if descriptive analysis find out discriminating items.

Comparison between treatment groups will be provided for the following parameters

- Time to parasitological clearance for the 1st episode (number of patients without parasite from D1 to D3)
- Time to fever clearance for the 1st episode (number of patients without temperature from D1 to D3)
- Proportion of patients without fever at D3 for repeated attacks
- Proportion of patients without parasite at D3 for repeated attacks
- Evolution of number of gametocyte carriers and mean values of gametocyte rate during the 42 days of follow-up for each episode
- Evolution of hemoglobin value for each patient during each attack (between D0 and D28) occurring during the 2 years of follow up
- Evolution of mean hemoglobin values at D0,D3, D7,D14 and D28 of each episode during the 2 years of follow up
- Evolution of Hackett score during the 2 years of follow up

The number of malaria attacks will be summarized by treatment group and overall.

The evolution of average duration between 2 attacks during the 2 years of follow up will be computed and analyzed using survival analysis methods.

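### Treatment incidence density is defined as a raw number of attacks with no child-time denominator, while observation time varies and the end of follow-up is stated in conflicting ways

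*Protocol*

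**What the plan says.** Section 6.2 names "Treatment incidence density" as a comparison between arms over the total follow-up of the cohort. Wherever the protocol makes this operational, it becomes a count:

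- Synopsis, evaluation criteria: "comparison of the number of malaria attacks between the two arms during the 2 years".
- Section 10.1.2: "Compare the number of malaria attack for each patient between two arms".
- Section 14.3.2.2 lists the number of attacks over the 2 years and labels that number treatment density.
- Section 14.5.3.2: "The number of malaria attacks will be summarized by treatment group and overall".

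The length of follow-up is stated in more than one way:

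- Section 7.2: "Each patient will be followed up actively after recruitment for 42 days (first follow up) and then passively for 2 years". The same section also says that participants are followed for 2 years.
- Section 8.1: "The duration of the study will be 2 years starting from the enrollment date of the first patient". It anticipates that recruitment will take four months.

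Section 12.2 lists seven reasons for leaving the cohort early, among them "Movement out of the study area for > 60 consecutive days", inability to be located for as long, withdrawn consent, and a serious adverse event that requires withdrawal.

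**The concern.** An incidence density is events divided by time at risk. The protocol uses that name and then specifies only the numerator. A child who leaves after six months with two attacks and a child who stays two years with two attacks count the same, although their attack rates differ fourfold.

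This goes beyond a modelling detail left for the statistical analysis plan. Section 14.1 makes Section 14 the basis of that plan, and Section 14.3.2.2 already equates the density with a count. The only tests named for a numeric variable (Section 14.5, t-test or Wilcoxon) take no account of observation time.

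If more children leave one arm, or leave it earlier, that arm shows fewer attacks even when the true rates are equal. The comparison could then be read as protection by one drug. The conflict over when follow-up ends adds to this, because it leaves undefined the child-time that a proper rate would need.

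**Working it through.** The protocol gives no attack rate, power or sample size for this variable, so there is no figure of its own to reproduce.

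**1. Observation time implied by the text**

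- Section 8.1: common close 24 months after the first enrolment, entry over 4 months. First child 24 months; last child 24 − 4 = 20 months; mean 22 with even recruitment.
- Section 7.2, 2 years per child: 24 months.
- Section 7.2, 42 days and then 2 years: 24 + 42/30.44 ≈ 25.4 months.

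For the last child enrolled the readings run from 20 to 25.4 months, and 25.4/20 = 1.27.

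**2. Effect of unequal withdrawal on raw counts**

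Suppose a share w of an arm leaves, each at a uniformly distributed point of the child's own follow-up. Mean observation time is then multiplied by 1 − w/2. With equal true rates, the expected ratio of mean counts is (1 − w₁/2)/(1 − w₂/2):

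- 10% v 10%: 0.95/0.95 = 1.00
- 20% v 10%: 0.90/0.95 = 0.947, about 5% fewer attacks
- 30% v 10%: 0.85/0.95 = 0.895, about 10% fewer attacks

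**3. False-positive rates by simulation**

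From the protocol: 200 children per arm, entry over 4 months, common close at 24 months, t-test or Wilcoxon at the two-sided 5% level. Assumed: 4 attacks per child-year in both arms, gamma variation between children with shape 2, Poisson counts given the child's rate, withdrawal as in step 2. There were 4,000 trials per row.

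| Withdrawal | Difference in mean count | t-test | Wilcoxon | Child-time rate ratio, robust variance |
|---|---|---|---|---|
| 10% v 10% | 0% | 4.8% | 5.1% | 5.2% |
| 20% v 10% | −5.4% | 10.3% | 12.4% | 5.6% |
| 30% v 10% | −10.4% | 23.4% | 33.0% | 5.3% |

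Repeat runs at these settings put the t-test at 23.4% to 25.5% in the last row.

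**4. Sensitivity to the assumptions**

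Rates of 2 or 5 attacks per child-year and gamma shapes of 1.5 or 4, with 2,000 trials per setting:

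- 15% v 15%: 4.3% to 5.5% on raw counts.
- 10% v 20%: 8.0% to 14.8% on raw counts.
- 5% v 25%: 17.5% to 46.2% on raw counts.
- Child-time rate ratio: 4.2% to 6.2% throughout.

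The pattern is stable. Raw counts hold their level when withdrawal is equal and lose it when withdrawal is unequal. Dividing by child-time brings the level back to about 5%.

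**The case against.** **Staggered entry is not bias.** A reader might infer that a last-enrolled child's shortfall of up to 4/24 = 17% biases the comparison. It does not. Randomisation spreads entry dates over both arms, so the 20-to-24-month spread only adds noise. The four months is itself only anticipated. This objection stands in full.

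**Overdispersion does not invalidate the t-test.** A reader might also infer that variation in attack rates between children breaks the t-test. The simulated counts are overdispersed, yet under equal withdrawal the test rejects about 5% of the time at 200 per arm. Overdispersion matters for choosing a rate model; it is not a fault in the planned test.

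**The harm depends on withdrawal that nobody has observed.** The protocol's only figure is 15% premature withdrawal (Section 14.2), given for the primary endpoint without a split by arm. It also acts to limit loss. Planned movers are excluded (Section 8.3.1), missed appointments are followed up at home (Section 9.9), and so is any 30-day silence (Section 13.3). Nor does Section 12.2 say that children leave for treatment-related events: its safety reason is any serious adverse event that requires withdrawal, without a condition of relatedness. This limits the claim to a conditional one. It does not show that withdrawal will be equal, since the trial is open and two of the reasons, serious adverse events and failure after rescue treatment, could depend on the drug.

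**Some of this belongs in the analysis plan.** The choice of model does, and no section assigns a specific test to the attack count; t-test or Wilcoxon is inferred from the general paragraph in Section 14.5. The definition is another matter, because the protocol fixes it in three places without a denominator.

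**Survival methods are already planned.** Section 14.5.3.2 applies them to the time between attacks, which concerns the same process and can handle censoring. That is a different variable and does not repair the comparison of counts.

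**Conclusion.** The point holds as a flaw of definition. The protocol calls the quantity a density, specifies a count, and gives inconsistent ends of follow-up from which child-time would have to be measured.

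The size of any distortion is conditional. Under the stated assumptions, withdrawal of 20% v 10% yields about 5% fewer attacks and about 10% false positives; 30% v 10% yields about 10% fewer and about 25%. Equal withdrawal yields no bias and the nominal 5%. The attack rate, the variation between children, the timing of exits and the split by arm are all assumptions, because the protocol gives none of them.

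The documents do not support saying that the comparison will be biased, only that it is unprotected if withdrawal differs. The variable is secondary, and its place at the head of the cohort objectives is list order without a stated hierarchy. The D28 non-inferiority analysis is untouched. The change should be made, but the trial's main conclusion does not depend on it.

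**What to change.** 1. **Definition.** In the Synopsis and Sections 10.1.2, 14.3.2.2 and 14.5.3.2, define treatment incidence density as attacks per child-year at risk. Count child-time from first treatment to the earliest of withdrawal, last contact or study close. State whether the index attack is counted, and whether the 14 days after each treatment count as time at risk, given that Section 7.2 handles recurrences in that window as failures and not as new episodes.
2. **Analysis.** Compare arms by a rate ratio with a 95% confidence interval, from a negative binomial model or a Poisson model with robust variance, with log child-time as offset. Report attacks, child-years and withdrawals by arm and by reason beside it.
3. **End of follow-up.** Reconcile Sections 7.2 and 8.1 to one rule, either a fixed period per child or a common calendar close.

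The cost is small. Enrolment, visit and withdrawal dates are already recorded, and no extra data or children are needed. The model can go into the statistical analysis plan, but the first and third changes alter protocol text and need a protocol clarification under the procedure in Section 26.

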# Flow Chart

## Study flow chart

| **STUDY PARAMETERS** | **REFERENCE DAYS FOR ALL ATTACKS** | | | | | | | | |  |
| --- | --- | --- | --- | --- | --- | --- | --- | --- | --- | --- |
| D0  V1  Inclusion visit | *D1**  *V2* | *D2**  *V3* | D3  V4  End of trt visit | D7  1d  V5 | D14  1d  V6 | D21  1d  V7 | D28  2d  V8 | D42 2d  V9  End of follow up visit | Un  sche  duled visit |
| Medical history | x |  |  |  |  |  |  |  |  |  |
| Age/Weight/Size/sex | x |  |  |  |  |  |  |  |  |  |
| Physical examination / Vital Signs | x | x | x | x | x | x | x | x | x | x |
| Clinical Tolerability: clinical signs | x | x | x | x | x | x | x | x | x | x |
| Parasitemia  thick and thin smear | x | x | x | x | x | x | x | x | x | x |
| Haemoglobin | x |  |  | x | x | x |  | x | x† | (x) |
| Platelets+ leukocytes + neutrophils | x |  |  |  | x | x |  | x | x† | (x) |
| Creatinemia | x |  |  |  | x | x |  | x | x† | (x) |
| ALT, total bilirubin | x |  |  |  | x | x |  | x | x† | (x) |
| Filter paper for PCR if thick smear + | x |  |  |  | (x) | (x) | (x) | (x) | (x) | (x) |
| Filter paper for DSAQ or L dosage | x# |  |  | x | x |  |  |  |  |  |
| AE record |  | x | x | x | x | x | x | x | x | x |
| Study treatment | x | x | x |  |  |  |  |  |  |  |
| Concomitant treatments | x | x | x | x | x | x | x | x | x | x |

* visits carried out at the 1st attack only

